## Abstract

**Background:**

Cervical spondylotic myelopathy (CSM) is the predominant cause of spinal cord dysfunction in the elderly. The patients are often frail and susceptible to complications. Posterior surgical techniques involving non-fusion are complicated by postlaminectomy kyphosis and instrumented fusion techniques by distal junction kyphosis, pseudarthrosis, or implant failure. The optimal surgical approach is still a matter of controversy.

Since anterior and posterior fusion techniques have been compared without presenting any superiority, the objective of this study is to compare stand-alone laminectomy with laminectomy and fusion to determine which treatment has the lowest frequency of reoperations.

**Methods:**

This is a multicenter randomized, controlled, parallel-group non-inferiority trial. A total of 300 adult patients are allocated in a ratio of 1:1. The primary endpoint is reoperation for any reason at 5 years of follow-up. Sample size and power calculation were performed by estimating the reoperation rate after laminectomy to 3.5% and after laminectomy with fusion to 7.4% based on the data from the Swedish spine registry (Swespine) on patients with CSM. Secondary outcomes are the patient-derived Japanese Orthopaedic Association (P-mJOA) score, Neck Disability Index (NDI), European Quality of Life Five Dimensions (EQ-5D), Numeric Rating Scale (NRS) for neck and arm pain, Hospital Anxiety and Depression Scale (HADS), development of kyphosis measured as the cervical sagittal vertical axis (cSVA), and death. Clinical and radiological follow-up is performed at 3, 12, 24, and 60 months after surgery. The main inclusion criterium is 1–4 levels of CSM in the subaxial spine, C3–C7. The REDcap software will be used for safe data management. Data will be analyzed according to the modified intention to treat (mITT) population, defined as randomized patients who are still alive without having emigrated or left the study after 2 and 5 years.

**Discussion:**

This will be the first randomized controlled trial comparing two of the most common surgical treatments for CSM: the posterior muscle-preserving selective laminectomy and posterior laminectomy with instrumented fusion. The results of the myelopathy randomized controlled (MyRanC) study will provide surgical treatment recommendations for CSM. This may result in improvements in surgical treatment and clinical practice regarding CSM.

**Trial registration:**

ClinicalTrials.gov
NCT04936074. Registered on 23 June 2021

**Supplementary Information:**

The online version contains supplementary material available at 10.1186/s13063-023-07123-4.

## Administrative information

Note: the numbers in curly brackets in this protocol refer to SPIRIT checklist item numbers. The order of the items has been modified to group similar items (see http://www.equator-network.org/reporting-guidelines/spirit-2013-statement-defining-standard-protocol-items-for-clinical-trials/).

## Introduction

### Background and rationale {6a}

Cervical spondylotic myelopathy (CSM) is characterized by weakness and paresthesia of the extremities, neck pain and stiffness, sphincter disturbance, and balance disorder. CSM is the most common cause of spinal cord dysfunction in the elderly [1] with an incidence of 41 per million in North America [2], peaking during the 7th decade of life. The male-to-female ratio is 2.7:1, and the most common level is C5–C6 [3].

CSM is typically the consequence of degenerative disc herniation, osteophyte formation, and hypertrophy of the ligamentum flavum that compress the spinal cord. Ossification of the posterior longitudinal ligament (OPLL), which is more prevalent in the Asian population, may also cause compression of the spinal cord. With non-operative treatments, i.e., medication and physiotherapy, 20–60% of the patients deteriorate neurologically and surgical treatment is therefore indicated [4].

The surgical treatment for CSM is decompression of the spinal cord. Decompression may be achieved with an anterior or posterior approach. Several algorithms have been proposed on whether to choose anterior discectomy and fusion, anterior corpectomy and fusion, posterior laminectomy with fusion, posterior laminoplasty, or posterior laminectomy alone [5, 6]. Anterior discectomy/corpectomy with fusion has been recommended in patients with a straight or kyphotic spine with compression of less than three levels [6]. A posterior approach has been recommended in patients with cervical lordosis and compression of more than three levels [7]. The World Federation of Neurological Societies (WFNS) Spine Committee modified these recommendations in 2019 towards a wider use of posterior approaches, e.g., in patients with posterior compression at 1 or 2 levels and patients with a flexible kyphosis [8]. It was recommended to address anterior compression with an anterior approach and posterior compression by a posterior approach.

A kyphosis leading to a cervical sagittal vertical axis (cSVA) of > 40 mm [9] (normal cSVA = 17–11 mm) [10] has been correlated to worse postoperative outcome in CSM patients, leading to the recommendation to correct kyphosis by an anterior approach [8]. In opposite to this, kyphosis correction has not shown to improve the clinical outcomes [11], indicating more remaining knowledge gaps concerning CSM patients with deformity.

Anterior and posterior decompression and fusion techniques have been compared with large sample sizes without presenting any difference in outcome [12, 13]. The question remains if fusion surgery is at all necessary as an adjunct to the decompression of the spinal cord and if CSM patients and, in that case, which CSM patients benefit from fusion surgery. After reports of postlaminectomy kyphosis in the 1970s and 1980s [14], prophylactic fusion has commonly been combined with the laminectomy procedure [12]. In a report from 1999, 34% of the patients developed kyphosis or swan neck deformity after laminectomy compared with 7% of patients surgically treated with laminoplasty, using a muscle-preserving technique [15].

A muscle-preserving technique that retains the facet integrity as well as the extensor musculature may also be used when performing posterior laminectomy. It has been observed to maintain sagittal balance after surgery without progression of kyphosis [16].

Posterior laminectomy as well as posterior laminectomy with fusion are both well-established surgical approaches. The most common surgical risks of both treatments are postoperative infection, dural tear, postoperative hematoma, neurologic deterioration, and C5 palsy. Specific risks of the muscle-preserving selective laminectomy are continuous degeneration of the affected level and progressive kyphotic deformity. Instrumented fusion may entail specific risks in terms of screw misplacement, implant failure, pseudarthrosis, increased surgical time, and blood loss [8]. Distal junction kyphosis (DJK) is a kyphotic angulation of at least 10° at the distal segment adjacent to a fused level and occurs in 24% of patients within a year after fusion surgery [17]. Adjacent segment pathology (ASP) is the progression of degeneration at the levels adjacent to a fused level and may also necessitate reoperation with laminectomy and extended fusion surgery [18].

In the lumbar spine, fusion surgery has been associated with increased operation times, blood loss, resource use, risk of complications, and 30-day mortality, when compared with laminectomy alone [19, 20]. A retrospective study in the cervical spine with a small sample size presented no differences in outcome between fusion or non-fusion groups after laminectomy, but increased operation time and blood loss in the fusion group [21].

There is yet to be investigated if the far more invasive fusion surgery is necessary to prevent the progression of deformity after decompression of the spinal cord or if the risk of DJK, pseudarthrosis, and implant failure after fusion surgery is more dangerous for these elderly and often frail patient group with CSM.

### Objectives {7}

The objective is to perform a non-inferiority study comparing posterior muscle-preserving selective laminectomy with laminectomy and fusion, to evaluate differences in outcome including reoperations, surgical complications, patient satisfaction, functional scores, and late degenerative changes including spondylolisthesis, kyphosis, and ASP.

We hypothesize that posterior muscle-preserving selective laminectomy is at least as successful in treating patients with CSM resulting in fewer reoperations, shorter hospital stay, and faster return to an active life, without reduced patient satisfaction, functional scores, or delayed kyphosis. Long-term follow-up radiographs and magnetic resonance imaging (MRI) are needed to assess differences in the subsequent degenerative changes including spondylolisthesis, kyphosis, and adjacent segment pathology (ASP) to compare the two strategies. Additionally, data from this study may be used to identify risk factors for the poor outcome to guide surgical decision-making.

### Trial design {8}

The MyRanc study is a multicenter randomized, controlled, parallel-group non-inferiority trial with 300 adult patients allocated in a ratio of 1:1 to two treatment groups: posterior muscle-preserving selective laminectomy (L-group) and laminectomy with instrumented fusion (LF-group).

## Methods: participants, interventions, and outcomes

### Study setting {9}

Participating centers are the University Hospitals of Uppsala (primary site), Stockholm and Gothenburg, and the County Hospital of RyHov in Jönköping. Each center has high volumes of CSM patients and complex spine surgery teams to provide the interventions.

### Eligibility criteria {10}

All patients diagnosed with CSM referred for a surgical consultation to the orthopedic or neurosurgery departments at the participating centers will be eligible for inclusion in the study. Patients will be enrolled if they meet the inclusion criteria (Table 1) and sign informed consent.

**Table 1 Tab1:** Inclusion and exclusion criteria

Inclusion criteria	Age >18 years
	1–4 levels of cervical spondylotic myelopathy in the subaxial spine, C3–C7, without or with deformity not exceeding exclusion criteria, see below
	Eligible for both treatments
	Ability to understand and read the Swedish language
	Symptomatic myelopathy with at least one clinical sign of myelopathy
	No previous cervical spine surgery or thoracic/lumbar spinal stenosis surgery
	Psychosocially, mentally, and physically able to fully comply with this protocol, including adhering to scheduled visits, treatment plan, completing forms, and other study procedures
	Personally, signed and dated informed consent document prior to any study-related procedures, indicating that the patient has been informed of all pertinent aspects of the trial
Exclusion criteria	Local kyphosis; a modified K-line minimum interval distance (INT) of <4 mm [22]
	Spondylolisthesis >4 mm and simultaneous translation >2 mm on lateral flexion/extension radiographs [23]
	Soft disc herniations only (no signs of osteophyte formation and hypertrophy of the ligamentum flavum)
	Active infection
	Neoplasm
	Trauma
	Inflammatory disease (i.e., rheumatoid arthritis or ankylosing spondylitis or DISH)
	Systemic infectious disease including HIV
	Lumbar or thoracic spinal disease to the extent that surgical consideration is probable or anticipated within 6 months after the cervical surgical treatment (significant lumbar stenosis as defined by Schizas C or worse) [24]
	OPLL
	Parkinson’s disease
	Drug abuse, dementia, or other reasons to suspect poor adherence to follow-up
	Previous cervical spine surgery

### Who will take informed consent? {26a}

The consultant spine surgeon informs the patient who is eligible for inclusion of the study and hands out the written participant information. The research personnel follows up with the consent form a few days later. In this way, the patient may take some time to deliberate and subtle coercion will be minimized.

### Additional consent provisions for collection and use of participant data and biological specimens {26b}

No other consent provisions are applicable; no biological specimens are collected.

## Interventions

### Explanation for the choice of comparators {6b}

Considering the existence of muscle-preserving laminectomy techniques that can maintain cervical lordosis [16], there are reasons to explore the additional value of instrumented fusion in the cervical spine. Although both methods are widely used, they are yet to be compared in a randomized controlled study.

### Intervention description {11a}

#### General set up

Under general anesthesia, the patient is placed in the prone position and the head is fixed in a clamp. The appropriate levels are verified by fluoroscopy when needed. Local anesthetics are applied to the planned incision site.

#### Muscle-preserving selective laminectomy

A posterior midline incision is made, and the nuchal fascia is divided longitudinally. The spinous process is split using a high-speed drill/ultrasound knife and without disturbing the bilateral deep extensor muscles, the spinous process is divided at its base. Laminectomy is performed with a width not extending more than 2 mm outside the dural borders. The bilateral facet joints are not exposed. Finally, the split fragments of the spinous process are sutured together [16]. No collar or restrictions will be used [25].

#### Posterior decompression and fusion

A midline incision is made over the appropriate levels, defined as the extension of laminectomy without extending beyond C3–C7 [26]. Soft tissue dissection and retraction are performed to identify osseous landmarks. Special care is taken to spare muscle attachments on C2 and C7. Spinal instrumentation is performed with lateral mass or pedicle screws (C3–C7) combined with rod fixation. Laminectomy is performed with a width not extending more than 2 mm outside the dural borders. Facet joint injury should be avoided. Special care is taken to spare the C7 spinous process and the distal half of the C7 lamina [27]. The sagittal alignment is corrected before spinal fixation. No collar or restrictions will be used [25].

### Criteria for discontinuing or modifying allocated interventions {11b}

Both stand-alone laminectomy and laminectomy with fusion have been performed on a regular basis for decades. Still, if severe adverse events are noted, the attending spine surgeon will contact the investigator of the study. Analysis of severe adverse events will be conducted to evaluate if the method is harmful and if the trial needs to be discontinued.

### Strategies to improve adherence to interventions {11c}

The representative from the steering committee on each research site as well as the coordinator and controller will monitor that the participants get their allocated surgical treatment. After the surgery procedure, the postoperative treatments are the same for both groups, so no further compliance to interventions is needed except for monitoring the indications for reoperations which are defined in the “Outcomes {12}” section.

### Relevant concomitant care permitted or prohibited during the trial {11d}

Postoperative care, pain control, and physiotherapy will be identical in both groups. Stiff neck collars that affect the range of motion are prohibited.

### Provisions for post-trial care {30}

The participants get no provision for participating in the trial. General standard insurance in case of malpractice and harm is provided by the Swedish healthcare system as well as any further post-trial care, if required.

### Outcomes {12}

The primary endpoint is reoperation for any reason at 5 years of follow-up. Reoperation will be considered in case of:Postoperative hematoma or reperfusion injury with neurologic deterioration within hours/days after the primary surgeryChange in sagittal alignment (kyphosis, DJK of more than 40 mm cSVA [9] and/or C2–C7 Cobb < −10°) with corresponding symptoms of camptocormia/increased pain/neurological deteriorationASP defined as degenerative changes on an adjacent level diagnosed with MRI and concomitant symptoms of myelopathy and/or radiculopathyImplant failure (clear radiolucency around >1 screw or rod breakage with increased neck pain and/or neurologic deterioration)Postoperative infection that requires revision surgery

Secondary outcome measures will be:Change from baseline in myelopathy score on the patient-derived modified Japanese Orthopaedic Association scale (P-mJOA) at 2 years of follow-upChange of at least 1 in mild myelopathy (>14 p), 2 in moderate myelopathy (12–14 p), and 3 in severe myelopathy (<12 p)Change from baseline in participant’s disability score on the Neck Disability Index (NDI) at 2 years of follow-upChange of at least 17% [28] in the NDI (0–100%) compared with baseline (adjustable according to results from own minimal clinically important change results for NDI)Change from baseline in myelopathy score on the Nurick scale at 2 yearsChange from baseline in the patient Quality of Life Five Dimensions (EQ-5D index) at 2 yearsChange from baseline in pain scores on the Numeric Rating Scale (NRS) at 2 yearsPain relief, as defined by ≥2.5 points [29] improvement on a 10-graded numeric rating scale for arm/shoulder painChange from baseline in the number of participants with psychological impairment on the Hospital Anxiety and Depression Scale (HADS) in both groups at 2 yearsThe cutoff for depression is defined as >10 p [30]Change in the number of satisfied participants on the satisfaction index in both groups at 2 yearsChange from baseline in myelopathy on the 10-s grip and release test at 2 yearsChange from baseline in myelopathy on the 10-s foot-tapping speed test at 2 yearsDifference in the number of participants with treatment adverse events in both groups at 5 yearsChange from baseline in sagittal alignment described as cSVA and C2–C7 Cobb angle in neutral radiographs at 5 yearsNumber of participants with a change in adjacent segment pathology (ASP) on MRIs from baseline to 5 years of follow-upNumber of participants with a change in compression of the spinal cord on the index level on MRIs from baseline to 5 years of follow-upChange in direct costs between the groups at 1 year of follow-upChange in indirect societal costs at 1 year of follow-upMortality at 5 years of follow-up

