#### Secondary outcomes

The P-mJOA (continuous variable) is a self-administered questionnaire with four domains, measuring motor (upper and lower extremities), sensor (upper extremities), and sphincter dysfunction in participants with CSM. The first domain is scored from 0 to 5, the second domain from 0 to 7, and third and four domains from 0 to 3. The maximum score is 18 points, indicating no deficits and the minimum score is 0, total tetraplegia. The minimum clinically important difference (MCID) in mJOA has been reported to be 2 overall with a threshold of 1 in mild myelopathy (mJOA >14), 2 in moderate myelopathy (mJOA 12–14), and 3 in severe myelopathy (mJOA <12) [36]. Consistency between P-mJOA and mJOA is demonstrated with identical mean scores and a SD of 1.5 together with a strong agreement of 0.83 with the use of the intraclass correlation coefficient and the Spearman correlation [37].

The NDI [28] (continuous variable) ranges from 0 to 100% with higher scores indicating severe disability. The MCID is 15–17% [28, 29, 38].

The Nurick scale (categorical variable) has six grades (0–5) based on the “difficulty in walking.”

EQ-5D index (continuous variable) ranges from −0.5 to 1 with higher scores reflecting a better quality of life [34]. The MCID is 0.24 [28].

EQ VAS (continuous variable) ranges from 0 to 100 with higher scores indicating better health.

NRS for neck and arm pain [29] (continuous variable) ranges from 0 to 10, with higher scores indicating more severe pain. The MCID is 2.5 for NRS of the neck and arm [29].

HADS (continuous variable) ranges from 0 to 42 with higher scores indicating more anxiety/depression with a cutoff for depression of >10 p [30].

The satisfaction index (categorical variable) evaluates the participants’ experienced overall result after surgery. The participant is asked “How is your attitude regarding the treatment result.” The alternative answers are “satisfied,” “uncertain,” and “dissatisfied.”

The 10-s grip and release test (continuous variable) is performed with the forearm in pronation and the wrist in mild extension. The participant is asked to grip and release with their fingers as rapidly as possible and the number of completed cycles of movement within 10 s is counted. Both hands are tested separately. The test has been correlated to the JOA score and differences between sex and age groups in the normal population have been set [39].

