## Statistical methods

### Statistical methods for primary and secondary outcomes {20a}

All endpoints will be analyzed in the modified intention to treat (mITT) population, defined as randomized patients who are still alive without having emigrated or left the study after 2 and 5 years.

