#### Secondary outcomes

The secondary outcomes will be analyzed using ordinal regression models, adjusted for sex. In addition, each secondary endpoint will be dichotomized and analyzed using logistic regression. The dichotomization will be done by comparing baseline and follow-up data, either based on MCID when applicable or else by defining success as an improvement from baseline. All secondary endpoints will be analyzed at 1, 2, and 5 years of follow-up, but not until the study is closed.

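### The pain, EQ-5D and (if 17% means scale points) NDI responder analyses score participants with no room to improve as certain failures in both arms

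*Protocol article*

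**What the plan says.** The responder rule has to be assembled from several sections of the protocol article.

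- **Outcomes {12}.** Pain relief for arm/shoulder pain is "as defined by ≥2.5 points [29] improvement on a 10-graded numeric rating scale". The NDI threshold is a change of at least 17% "in the NDI (0–100%) compared with baseline", and it may be revised in the light of the trial's own MCID work. P-mJOA thresholds are 1, 2 or 3 points, graded by severity.
- **Plans for assessment and collection of outcomes {18a}, Secondary outcomes.** The NRS "ranges from 0 to 10, with higher scores indicating more severe pain", with an MCID of 2.5 for neck and arm. The EQ-5D index has a maximum of 1 and an MCID of 0.24. For P-mJOA, "The maximum score is 18 points, indicating no deficits".
- **Statistical methods {20a}.** On the population: "All endpoints will be analyzed in the modified intention to treat (mITT) population". Secondary outcomes go first into ordinal regression adjusted for sex. In addition, each is dichotomised for logistic regression, "either based on MCID when applicable or else by defining success as an improvement from baseline".
- **Eligibility criteria {10}, Table 1.** The symptom requirement is "Symptomatic myelopathy with at least one clinical sign of myelopathy". No minimum NRS, NDI or EQ-5D impairment is listed.

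**The concern.** A fixed improvement threshold needs a baseline that leaves space for it. Signs of myelopathy do not require arm pain, so a participant can enter with an arm-pain NRS of 0, stay pain-free for the whole trial and still be scored a failure for pain relief. Such participants carry no information about which operation relieves pain better, yet they sit in both denominators.

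That pulls the two responder rates together and lowers the chance of seeing a real difference. The direction matters here because the Objectives hypothesise that laminectomy does not reduce satisfaction or functional scores. A responder table diluted towards no difference would read as mild support for that hypothesis.

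**Working it through.** **The plan's own power figure.** The article states power only for reoperation. Analysable N = 300 × (1 − 0.163 − 0.05) = 236.1, or 118 per arm. With 3.5% vs 7.4% and a 5-point margin, the distance is 0.05 + 0.039 = 0.089. SE = √[(0.035 × 0.965 + 0.074 × 0.926)/118] = 0.0294. Power = Φ(0.089/0.0294 − 1.96) = 85.6%, which agrees with the stated 86%. A simulation of the shifted-outcome permutation test (not blocked on sex) gave about 87.5%. None of this involves the responder endpoints, for which no power is stated.

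**Room to improve on each scale.**

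| Scale | Best score | Required change | Baselines that cannot succeed |
|---|---|---|---|
| NRS pain (whole numbers) | 0 | 2.5 | 0, 1, 2 |
| EQ-5D index, if 0.24 is used | 1 | 0.24 | above 1 − 0.24 = 0.76 |
| NDI, if 17% means scale points | 0 | 17 | below 17 |
| NDI, if 17% is relative to baseline | 0 | 17% of own score | essentially only 0 |
| P-mJOA | 18 | 1 (>14), 2 (12–14), 3 (<12) | 18 only |

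For P-mJOA, the tightest case in each band still fits: 18 − 17 = 1, 18 − 14 = 4, 18 − 11 = 7.

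**Effect on the comparison.** Let f be the share of each arm without room, and p₁ and p₂ the responder rates among those with room, with difference d and mean p̄.

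- All participants: rates p(1 − f), difference d(1 − f), n per arm.
- Restricted: rates p, difference d, n(1 − f) per arm.

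With the pooled variance, expected z² is n·d²(1 − f)/[2p̄(1 − p̄(1 − f))] for all participants and n·d²(1 − f)/[2p̄(1 − p̄)] when restricted. The ratio, restricted to all, is (1 − p̄(1 − f))/(1 − p̄). It exceeds 1 whenever f > 0, so restriction gains power despite the smaller n. At p̄ = 0.525 and f = 0.3 it is 0.6325/0.475 = 1.33.

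**Size under assumptions.** The documents give neither f nor responder rates, so both are assumed. Power = Φ[(|d| − 1.96·SE₀)/SE₁], with SE₀ pooled and SE₁ unpooled, two-sided 5%, 118 per arm:

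| Rates with room | f | Difference, all (restricted) | OR, all (restricted) | Power, all | Power, restricted |
|---|---|---|---|---|---|
| 60% vs 45% | 10% | 13.5 (15.0) pp | 1.72 (1.83) | 54.7% | 59.2% |
| 60% vs 45% | 30% | 10.5 (15.0) pp | 1.57 (1.83) | 38.6% | 48.8% |
| 60% vs 45% | 50% | 7.5 (15.0) pp | 1.48 (1.83) | 25.7% | 37.0% |
| 70% vs 50% | 10% | 18.0 (20.0) pp | 2.08 (2.33) | 79.6% | 85.0% |
| 70% vs 50% | 30% | 14.0 (20.0) pp | 1.78 (2.33) | 58.7% | 75.1% |
| 70% vs 50% | 50% | 10.0 (20.0) pp | 1.62 (2.33) | 38.8% | 60.4% |
| 40% vs 25% | 10% | 13.5 (15.0) pp | 1.94 (2.00) | 62.7% | 64.8% |
| 40% vs 25% | 30% | 10.5 (15.0) pp | 1.83 (2.00) | 48.5% | 54.0% |
| 40% vs 25% | 50% | 7.5 (15.0) pp | 1.75 (2.00) | 34.4% | 41.2% |

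The gain runs from 64.8 − 62.7 = 2.1 to 60.4 − 38.8 = 21.6 points. Not all the lost power returns: at 60% vs 45% with f = 0 it would be 63.7%.

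The 118 per arm reflects five-year mortality, whereas the patient-reported change outcomes are listed at two years. With 142 per arm (5% loss, no deaths) the corresponding extremes are 70.8% to 72.8% and 45.1% to 68.5%, gains of 2.0 and 23.4 points.

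**The case against.** **It touches few scales.** This stands. A reader might infer that every responder comparison is diluted. The documents do not support that. P-mJOA, listed first among the secondary outcomes, can reach its graded threshold from every score except 18, a score that means no deficits and is hardly compatible with the entry requirement. The HADS cutoff and the satisfaction index are not MCID-improvement rules.

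**NDI and EQ-5D are conditional.** This also stands. The NDI wording can be read as relative to baseline, although the 0–100% range beside it and the MCID of 15–17% given with that scale favour points. Outcomes {12} sets no EQ-5D threshold; 0.24 enters only through the rule to use an MCID where applicable.

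**The responder analysis is supplementary.** True. Ordinal regression is named first and keeps everyone, so power for the secondary outcomes does not rest on these tables. The non-inferiority test and its margin apply to reoperation alone, and no rule turns a null secondary result into a claim.

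**The proportion of all patients reaching an MCID is a legitimate quantity.** It is, and it should still be reported. As a comparison of two operations, though, it is less sensitive, and scoring a pain-free participant as a failure of pain relief is hard to defend.

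**The analysis plan may settle the denominator.** That certain failures are counted is inferred from the sections together, not stated outright. But the article fixes both the population for all endpoints and the dichotomisation rule, so a plan that narrowed the denominator would depart from it.

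**Conclusion.** The point holds for NRS pain, for EQ-5D if 0.24 is the threshold, and for NDI if 17% means scale points. On those scales, participants without room are certain failures in both arms. The risk difference and odds ratio shrink and some power is lost. The direction follows from the stated rules. The size does not: the 2 to 22 power points rest on assumed shares of 10–50%, assumed responder rates and 118 per arm, and at a 10% share the gain is only about 2 to 5 points.

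It would be wrong to conclude that the secondary outcomes as a whole lose power, or that the non-inferiority conclusion or its 86% power is affected. This is a modest defect in supplementary analyses, worth correcting because correction is cheap.

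**What to change.** In Outcomes {12} and in the secondary-outcome part of Statistical methods {20a}:

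1. Run the MCID responder logistic regressions for NRS, EQ-5D and NDI among mITT participants whose baseline permits the threshold: NRS at least 3, EQ-5D at most 0.76, NDI at least 17.
2. State that the NDI 17% is in scale points. If the trial's own MCID later replaces 17, the baseline cut moves with it.
3. Keep all participants in the ordinal analysis.
4. Report the all-participant responder proportion descriptively beside the restricted comparison.

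The restriction preserves the randomised comparison as long as it uses a value recorded before allocation is known. The article says baseline data are collected before the intervention and places both baseline and allocation in the enrolment period, so one sentence fixing that order would help.

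The cost is a wording change and smaller denominators that differ by scale in the responder tables. The secondary analyses wait until the study is closed, so the change can still be prespecified.
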